**NB: FOR REPORTED SEVERE SIDE EFFECT, COMPLETE THE QUESTIONS UNDER 4.3**

- 3.3. **Adverse events after taking the three drugs be captured in the questions that follows:** defined as; **1 = mild:** easily tolerated, does not interfere with daily activity, **2 = moderate :** uncomfortable enough to interfere with daily activity, **3 = severe :** precludes daily activity,

| Adverse Events after taking the three drugs |                                 |                                    |    |    |    |    |    |    |    |    |     |     |     |     |     |     |     |
|---------------------------------------------|---------------------------------|------------------------------------|----|----|----|----|----|----|----|----|-----|-----|-----|-----|-----|-----|-----|
| Symptoms/signs                              |                                 | when did the side effects appeared |    |    |    |    |    |    |    |    |     |     |     |     |     |     |     |
|                                             |                                 | Evaluation                         |    |    |    |    |    |    |    |    |     |     |     |     |     |     |     |
|                                             |                                 | D1                                 | D2 | D3 | D4 | D5 | D8 | D2 | D8 | D9 | D10 | D11 | D12 | D13 | D14 | D15 | D30 |
| 4..2.1                                      | Fever                           |                                    |    |    |    |    |    |    |    |    |     |     |     |     |     |     |     |
| 4.2.2                                       | Itching/ground itch             |                                    |    |    |    |    |    |    |    |    |     |     |     |     |     |     |     |
| 4.2.3                                       | Headaches                       |                                    |    |    |    |    |    |    |    |    |     |     |     |     |     |     |     |
| 4.2.4                                       | Dizziness                       |                                    |    |    |    |    |    |    |    |    |     |     |     |     |     |     |     |
| 4.2.5                                       | Tiredness                       |                                    |    |    |    |    |    |    |    |    |     |     |     |     |     |     |     |
| 4.2.6                                       | Deafness                        |                                    |    |    |    |    |    |    |    |    |     |     |     |     |     |     |     |
| 4.2.7                                       | Jaundice                        |                                    |    |    |    |    |    |    |    |    |     |     |     |     |     |     |     |
| 4.2.8                                       | Weakness                        |                                    |    |    |    |    |    |    |    |    |     |     |     |     |     |     |     |
| 4.2.9                                       | Fatigue                         |                                    |    |    |    |    |    |    |    |    |     |     |     |     |     |     |     |
| 4.2.10                                      | Nausea                          |                                    |    |    |    |    |    |    |    |    |     |     |     |     |     |     |     |
| 4.2.11                                      | Vomiting                        |                                    |    |    |    |    |    |    |    |    |     |     |     |     |     |     |     |
| 4.2.12                                      | Diarrhoea                       |                                    |    |    |    |    |    |    |    |    |     |     |     |     |     |     |     |
| 4.2.13                                      | Abdominal pain                  |                                    |    |    |    |    |    |    |    |    |     |     |     |     |     |     |     |
| 4.2.14                                      | Flatulence/dyspepsia            |                                    |    |    |    |    |    |    |    |    |     |     |     |     |     |     |     |
| 4.2.15                                      | Constipation                    |                                    |    |    |    |    |    |    |    |    |     |     |     |     |     |     |     |
| 4.2.16                                      | Joint/muscular pain             |                                    |    |    |    |    |    |    |    |    |     |     |     |     |     |     |     |
| 4.2.17                                      | Swelling of (upper/lower) limbs |                                    |    |    |    |    |    |    |    |    |     |     |     |     |     |     |     |

- 4.2.18 Swelling of eyelids/abnormal feeling in the eyes
- 4.2.19 Rash/plaque
- 4.2.20 Scrotal reaction
- 4.2.21 Skin nodules
- 4.2.22 Worm expulsion
- 4.2.23 Haematuria
- 4.2.24 Lymphoedema
- 4.2.25 Elephantiasis
- 4.2.26 Hydrocele
- 4.2.27 Palpitation/tachycardia
- 4.2.28 Orthostatic hypotension
- 4.2.29 Others
- 4.2.30

If other specify.....  
 .....  
 .....  
 .....

**NB: FOR REPORTED SEVERE SIDE EFFECT, COMPLETE THE QUESTIONS UNDER 4.3**

## Appendix 5: SAEs recording form

1.7. Community ID: | | | | | | | | | |

1.8. Participant ID | | | | | | | | | | | | | | | |

### 3.4. SAEs form between D1 and D15; use the codes 1 = Severe, 2 = Very severe

| Severe effects |                                         | Days when serious side effects occurred |    |    |    |    |    |    |    |    |    |     |     |     |     |     |     |     |
|----------------|-----------------------------------------|-----------------------------------------|----|----|----|----|----|----|----|----|----|-----|-----|-----|-----|-----|-----|-----|
|                |                                         | D0                                      | D1 | D2 | D3 | D4 | D5 | D6 | D7 | D8 | D9 | D10 | D11 | D12 | D13 | D14 | D15 | D30 |
| 4.3.1          | Angioneurotic oedema/anaphylactic shock |                                         |    |    |    |    |    |    |    |    |    |     |     |     |     |     |     |     |
| 4.3.2          | Anuresis                                |                                         |    |    |    |    |    |    |    |    |    |     |     |     |     |     |     |     |
| 4.3.3          | Seizures                                |                                         |    |    |    |    |    |    |    |    |    |     |     |     |     |     |     |     |
| 4.3.4          | Erythema multiforme                     |                                         |    |    |    |    |    |    |    |    |    |     |     |     |     |     |     |     |
| 4.3.5          | Epidermal necrolysis                    |                                         |    |    |    |    |    |    |    |    |    |     |     |     |     |     |     |     |
| 4.3.6          | Recurrent symptoms                      |                                         |    |    |    |    |    |    |    |    |    |     |     |     |     |     |     |     |
| 4.3.7          | Stevens Johnson Syndrome                |                                         |    |    |    |    |    |    |    |    |    |     |     |     |     |     |     |     |
| 4.3.8          | Others                                  |                                         |    |    |    |    |    |    |    |    |    |     |     |     |     |     |     |     |
| 4.3.9          | If other specify.....                   |                                         |    |    |    |    |    |    |    |    |    |     |     |     |     |     |     |     |
|                | .....                                   |                                         |    |    |    |    |    |    |    |    |    |     |     |     |     |     |     |     |
|                | .....                                   |                                         |    |    |    |    |    |    |    |    |    |     |     |     |     |     |     |     |

**AFTER COMPLETING QUESTIONS UNDER 4.3 AND 4.2, THE INVESTIGATOR SHOULD ANSWER THE FOLLOWING QUESTION; THE ANSWER WILL BE YES IF ANY SEVERE EFFECT IS WAS REGISTERED**

3.5. Did the interviewed participant experience a serious/severe adverse event after taking the 3 drugs? 1. Yes 2. No 99. unknown

3.6. If yes for 4.5, please list down.....

3.7. If yes for 4.5, please complete the Fever and serious adverse events **surveillance form appendix 2.**

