**On Day 17, 18**, the clinical nurses and HEW from each of the original four teams will perform one last house to house follow up of all the households that received the triple drug administration. (400 HH x 4 teams = 1600 HH) This will be the last active follow-up step.

**Day 19-30**, the HEWs will maintain the reporting form for another two weeks in the event of any additional complaints from the targeted beneficiaries. This will be completely passive and the HEW will only log complaints if they are reported by a beneficiary. On Day 30, all of the co-administration registers and forms will be collected for data analysis from the HEWs.

Note that in the “standard MDA” control arm, the process described above will be conducted twice. First, IVM/ALB MDA will take place for with 14 days of active surveillance then the Trachoma MDA will take place for 14 days of active surveillance. Passive surveillance will continue in the control arm for two weeks after that.

Once the 45th day of the study is reached in Oromia, the field implementation portion of the study will be complete. The DSMB will review the final data before making a recommendation on how the remainder of the population in the woreda should be treated. Should the DSMB and the FMOH agree, the remaining 4-5000 beneficiaries within Homesha will be targeted for co-administration. However, at this juncture, the RCT will be over. The study will move to strictly observational with the same enhanced supervision in place.

Table 3: Follow up Schedule for both the Trial and the Control Arms of the Study

|                                                    | Day 1 | Day 2 | Day 3 | Day 4 | Day 5 | Day 6 | Day 7 | Day 8 | Day 9 | Day 10 | Day 11 | Day 12 | Day 13 | Day 14 | Day 15 | Day 16 | Day 17 | Day 18 | Day 19-30 | Day 31 |
|----------------------------------------------------|-------|-------|-------|-------|-------|-------|-------|-------|-------|--------|--------|--------|--------|--------|--------|--------|--------|--------|-----------|--------|
| Actual Distribution                                |       |       |       |       |       |       |       |       |       |        |        |        |        |        |        |        |        |        |           |        |

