## 10 Timetable for Study Completion

[figure not shown]

The Primary outcome is

- The safety as can be measured by incidence of AEs/SAEs over one month following the co-administered MDA in comparison to a control group receiving the standard MDA regimen.

Secondary Outcomes are:

- Understanding the perceptions of the beneficiaries receiving the co-administration of azithromycin, ivermectin, and albendazole especially surrounding pill burden and the change in MDA distribution schedule.
- Understanding the perceptions of the co-administration strategy by the local health workforce as a means of PC-NTD drug delivery.
- A cost analysis comparing existing MDA unit costs from woredas within the region already on a standard MDA schedule with that of the co-administered woredas.

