## Appendix 4: AES Surveillance form

- 3.1. Community ID: |\_\_|\_|\_|\_|\_|\_|\_|\_|\_|\_|\_|
- 3.2. Participant ID |\_\_|\_|\_|\_|\_|\_|\_|\_|\_|\_|\_|
- 3.2.1. Dates of first filling-in for surveillance purposes |\_\_DD|\_\_MM|\_\_YY|
- 3.2.1.1. Which day(s), please underline D1, D2, D3, D4, D5, D6, D7, D8, D9, D10, D11, D12, D13, D14, D15, D16, D17, D18, D19, D20, D21, D22, D23, D25, D26, D27, D28, D29, D20
- 3.2.2. Place of first filling-in? 1. Survey site 2. Home 3. Other 99. unknown
- 3.2.3. If other in 4.1.2., specify the place.....
- 3.2.4. Did you take all the three drugs? 1. Yes 2. No 99. unknown
- 3.2.5. Did you regurgitate the drugs? 1. Yes 2. No 99. Unknown
- 3.2.6. When did you take the drugs? |\_\_DD|\_\_MM|\_\_YY|
- 3.2.7. How did you feel after taking the drugs? 1. Fine (better than before) 2. Same as before 3. Bad 98. Do not know
- 3.2.7.1. If the respondent says **fine (better than before)** for 4.1.8, review questions under 2.1 “**For complaints or events prior to the treatment**” to describe their evolution. Use the coding; 0 = **None**: the complaint has gone, 1=**Improved**: the complaint is significantly less than before the treatment, 2 = **Ongoing**: the complaint is the same as before the treatment, 3 = **Exacerbated**: the complaint increased after the treatment; to grade them as in the list below

| Events existing before the treatment |                     | complaints (tick as necessary) | Grade |
|--------------------------------------|---------------------|--------------------------------|-------|
| 4.1.8.1.1                            | Fever               |                                |       |
| 4.1.8.1.2                            | Itching/ground itch |                                |       |
| 4.1.8.1.3                            | Headaches           |                                |       |
| 4.1.8.1.4                            | Dizziness           |                                |       |
| 4.1.8.1.5                            | Tiredness           |                                |       |
| 4.1.8.1.6                            | Deafness            |                                |       |
| 4.1.8.1.7                            | Jaundice            |                                |       |
| 4.1.8.1.8                            | Weakness            |                                |       |
| 4.1.8.1.9                            | Fatigue             |                                |       |

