| 4.1.8.1.10                           | Nausea              |                                |       |
| 4.1.8.1.11                           | Vomiting            |                                |       |
| 4.1.8.1.12                           | Diarrhoea           |                                |       |
| 4.1.8.1.13                           | Abdominal pain      |                                |       |

- 4.1.8.1.14 Flatulence/dyspepsia
- 4.1.8.1.15 Constipation
- 4.1.8.1.16 Joint/muscular pain
- 4.1.8.1.17 Swelling of (upper/lower) limbs
- 4.1.8.1.18 Swelling of eyelids/abnormal feeling in the eyes
- 4.1.8.1.19 Rash/plaque
- 4.1.8.1.20 Scrotal reaction
- 4.1.8.1.21 Skin nodules
- 4.1.8.1.22 Worm expulsion
- 4.1.8.1.23 Haematuria
- 4.1.8.1.24 Lymphoedema
- 4.1.8.1.25 Elephantiasis
- 4.1.8.1.26 Hydrocele
- 4.1.8.1.27 Palpitation/tachycardia
- 4.1.8.1.28 Orthostatic hypotension
- 4.1.8.1.29 Others
- 4.1.8.1.30 **If other specify**.....
- .....
- .....

3.2.7.2. Did the respondent experience complaints after taking the 3 drugs? 1. Yes 2. No  
99. unknown

3.2.7.3. If yes, which one(s)? (See questions under 4.1.8.1).....  
.....  
.....

**3.2.7.4.** How would you qualify your main complaint (see questions under 4.1.8.2), after taking the 3 drugs **1 = Improved 2 = Ongoing 3 = Exacerbated 4= Resolved**

3.2.7.5. If the respondent says **Bad (worsened than before treatment) for 4.1.8**, review questions under 2.1 “**For complaints or events to prior to the treatment**” to describe **their evolution**. Use the coding; 0 = **did not feel sick**, 1=**mild**, 2 = **Moderate**, 3 = **Major/severe**; to grade them as in the list below

3.2.7.6.

| Adverse event due to worsened existing symptoms before treatment |                                    |            |      |
|------------------------------------------------------------------|------------------------------------|------------|------|
| Symptoms/signs                                                   | when did the side effects appeared | Evaluation | Code |

|            |                                                  | D1 | D2 | D3 | D4 | D5 | D8 | D2 | D8 |
|------------|--------------------------------------------------|----|----|----|----|----|----|----|----|
| 4.1.8.5.1  | Fever                                            |    |    |    |    |    |    |    |    |
| 4.1.8.5.2  | Itching/ground itch                              |    |    |    |    |    |    |    |    |

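### The adverse-event onset grids have no columns for D16 to D29 and do not define D, so they fit neither the one-month primary outcome nor the follow-up schedule

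*Protocol*

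**What the plan says.** Section 10 defines the primary outcome as "The safety as can be measured by incidence of AEs/SAEs over one month following the co-administered MDA", compared with the control group.

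Section 8.8 sets the follow-up that should supply it. There are next-day visits through Day 14, a final house-to-house round on Days 17-18 ("This will be the last active follow-up step"), and passive logging by health extension workers over Days 19-30. Table 4 in Section 8.9 repeats this, with separate rows that include Days 17+18 and Days 19-30.

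The forms that receive these data use day columns:

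- Serious events (Appendix 5, item 3.4): titled "SAEs form between D1 and D15; use the codes 1 = Severe, 2 = Very severe", with columns from D0 that end "D9 | D10 | D11 | D12 | D13 | D14 | D15 | D30".
- New events (Appendix 4, item 3.3): columns from D1 that continue "D5 | D8 | D2 | D8 | D9 | D10 | D11 | D12 | D13 | D14 | D15 | D30".
- Worsened pre-existing symptoms (Appendix 4, item 3.2.7.6): "D1 | D2 | D3 | D4 | D5 | D8 | D2 | D8", with nothing later.

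Appendix 4 also opens with a list of days on which the form may be filled in (item 3.2.1.1). That list does run past D15: "D13, D14, D15, D16, D17, D18, D19, D20, D21, D22, D23, D25, D26, D27, D28, D29, D20".

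**The concern.** The outcome, the visit schedule and the fill-in list all expect reports after D15, but the grids that hold onset day and severity leave a gap from D16 to D29. The worsened-symptom grid stops sooner still.

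Severity matters as well as dating. The mild, moderate and severe grades for new events sit in the grid of item 3.3. Section 8.9 reports severity and uses it as a covariate in the regression, and Section 8.5 treats a severe event as a possible serious one that prompts contact with the monitoring board. A late event with no grid cell has no structured onset day or grade to feed any of these.

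Because D is undefined, two field teams could enter the same event under different columns, or one could find a column where the other finds none. In a comparison with a 1.5-point margin, the two arms need to be recorded in the same way.

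**Working it through.** **1. Columns against Days 1-30.** The charitable count reads the misprinted run of D8, D2, D8 as D6, D7, D8.

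| Item | Days 1-30 without a column, as printed | Charitable reading |
|---|---|---|
| 3.4 serious events | D16-D29: 14 | 14 |
| 3.3 new events | D6, D7, D16-D29: 16 | D16-D29: 14 |
| 3.2.7.6 worsened symptoms | D6, D7, D9-D30: 24 | D9-D30: 22 |
| 3.2.1.1 fill-in list | D24, D30: 2 | D24: 1 (last D20 read as D30) |

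For new and serious events the gap is 14/30 = 47% of the outcome days, and it does not depend on how the misprint is read. For worsened symptoms it is 22/30 = 73% on the charitable reading. That figure is less certain, because it rests on a garbled header.

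**2. What the Days 17-18 visit becomes on the form.** If D is study day, the whole visit falls in the gap. If D is days since dose, a person dosed on study day t is visited at D = 17 - t and 18 - t when the dosing day is D0, or one more when it is D1:

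| Dosed on Day | D0 = dosing day | D1 = dosing day |
|---|---|---|
| 1 | D16, D17 | D17, D18 |
| 3 | D14, D15 | D15, D16 |
| 5 | D12, D13 | D13, D14 |
| 7 | D10, D11 | D11, D12 |
| 9 | D8, D9 | D9, D10 |
| 11 | D6, D7 | D7, D8 |
| 13 | D4, D5 | D5, D6 |

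On this reading the visit reaches the gap only for people dosed on Day 1 and, with D1 numbering, Day 3. The other five batches stay within the printed columns.

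**3. Control arm.** Azithromycin follows ivermectin/albendazole by about two weeks. If D runs from the first dose, azithromycin is given at D14 (D0 numbering) or D15 (D1 numbering). Columns D16-D29 then correspond to days 2-15 or days 1-14 after azithromycin, so nearly all of that round's early follow-up has no cell. If D restarts at each round, the early days do have cells. Section 8.8 says the process is carried out twice but not whether the day count restarts.

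**4. Direction of any effect.** Let q1 and q0 be the fractions of people with an adverse event who end up counted as having none, in the trial and control arms. With the planning rates of 8.5% and 7% (Section 8.1), the observed difference in percentage points is

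8.5(1 - q1) - 7(1 - q0) = 1.5 - 8.5·q1 + 7·q0.

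Equal losses shrink it. Control losses more than 8.5/7 = 1.21 times the trial-arm losses enlarge it. The protocol gives no basis for either q, and both may be zero if the free-text items are used well.

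**The case against.** The strongest reply is that a late event does have somewhere to go. Items 3.2.7.2 to 3.2.7.4 ask about any complaint after treatment, name it in free text and describe how it evolved, with no day limit. Items 3.5 and 3.6 do the same for severe or serious events, and item 3.2.1.1 lets the form be marked for almost every day to D29. Section 8.9 analyses the proportion of people with an event, which needs no onset day. The D30 column may be meant to collect the passive interval, since the team returns at one month. The forms are also provisional: a note before Appendix 2 says they are to be merged into one register and made electronic.

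Much of this stands, and it rules out several stronger readings that a reader might infer:

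- *Late events have nowhere to be recorded.* Not so; they can be noted, but without an onset day or a grid severity grade.
- *Item 3.5 turns to no for a late severe event.* The instruction says when the answer is yes. It does not say that only grid entries count, and the question itself has no day limit.
- *The gap favours non-inferiority.* That needs roughly equal proportional losses. Heavier loss in the control arm would work the other way.
- *The Days 17-18 visit is unrecordable.* This holds for everyone only if D is study day.
- *The gap is 58% of trial-arm follow-up.* Taking dosing on Days 1, 3, ..., 13 and follow-up to Day 30, the gap covers 98 of 168 person-days (58%) by study day, or 56 of 161 (35%) by days since dose. The two denominators differ, since the first counts the dosing day. These are shares of time, not of events, and the protocol gives no onset distribution.

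The reply does not remove the mismatch itself. A fill-in day is not an onset day. Item 3.2.7.4 records evolution, not severity. No text assigns D16-D29 to the D30 column, and the serious-event header asks for the days on which effects occurred. Conversion to the electronic system will carry the gap over unless someone corrects it.

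**Conclusion.** The point holds as a mismatch between the recording forms and the outcome they serve. The new-event and serious-event grids have no onset-and-severity cell for D16-D29, 14 of the 30 outcome days. The worsened-symptom grid ends at about D8, subject to the misprinted header. D is undefined, and the grids start at different days. The 14-day count rests on the printed column headers and, for serious events, is supported by the form's own title.

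The consequence is that late events cannot be dated by onset and graded by day in a structured way, and that capture could differ between arms if days run from the first dose. Whether any events would be lost, how many, and in which direction the comparison would move cannot be determined from the protocol. The change is worth making because the forms feed the primary outcome and can still be edited cheaply.

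**What to change.** In the combined register and its ODK version:

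- Replace the day columns in items 3.2.7.6, 3.3 and 3.4 with an onset date and a severity grade for every event, whether new, worsened or serious, over the full one-month window.
- Define D0 as the dosing day on all forms. In the control arm, do so for each dosing round, so that days since dose can be derived in the same way in both arms.
- Retitle the serious-event form to cover the full window.
- If any day columns are kept, add D16-D29 and correct the D6/D7 misprints. Also correct the missing D24 and the final D20 in item 3.2.1.1.

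The cost is a form edit before launch, with no extra visits or participants.
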